### Dosing

Lithium carbonate will be started at 300 mg at bedtime. After 3 days, participants will be advised to increase the dosage to 600 mg, and then the dose will be titrated as clinically appropriate to maximum well-tolerated doses based on blood levels. Subsequent adjustments will be made at the discretion of the treating clinician, considering patient tolerability, response, and other medications included in treatment as part of TAU. Clinicians may increase the dose as clinically indicated and tolerated, not to exceed serum levels of 1.2 mEq/L. Clinicians will be discouraged from any dose increases that are expected to result in unacceptable tolerability. Similarly, at any time during study participation, if the 600 mg/day dose is not tolerated, the dose may be decreased to a minimum of 300 mg/day. Patients who cannot tolerate 300 mg/day of lithium will continue to receive TAU and otherwise adhere to study protocol and procedures for the duration of the trial. Treating psychiatrists will be asked to manage the patients as they would any other patient, adjusting medications as needed in response to clinical exacerbations or side effects.

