### Valproate crossover

Participants who are unable to tolerate lithium or fail to achieve relapse prevention on lithium will be crossed over to treatment with valproic acid in an identically designed second phase, including a 3-month stabilization phase, 1-month observation phase, and a relapse prevention phase of up to 24 months. Measurement of valproate response in a subset of subjects will make it possible to test whether SNPs associated with lithium response are also associated with valproate response.

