We will also examine repeated quantitative measures of depressive or manic symptoms taken at regular intervals over the period of follow-up. This will address the number of symptoms subjects continued to suffer even when they were considered in remission. For the repeated measures analyses, we will use longitudinal data methods to associate SNPs with differences in symptom measures over time. In particular, we will use linear regression models with general estimating equations (GEE) to account for the correlation engendered by repeated measures on the same participants. We will explore the repeated measures data to diagnose the nature of this correlation and then treat it as a nuisance variable in the model. We will then test whether the SNPs identified in the Retrospective Study or other retrospective datasets (ConLiGen) are significantly associated with differences in mean scores on the measures of depressive or manic symptoms, controlling for time of assessment, age, sex, clinical site, and the same quantitative indices of ancestry as the in the Cox model if deemed necessary. We will further explore for possible interactions between the SNP and time to test whether the effect of the SNP on depressive or manic symptoms changes over time.

To determine whether the effects of SNPs found to be associated with response in these analyses are specific to lithium treatment, we will use two strategies. First, in the time to event and repeated measures analyses described above, we will examine whether the inclusion of a covariate describing prior disease episode frequency affects the estimated association between SNPs and clinical relapse and/or symptom differences. If the estimated association is mitigated, this will suggest that the SNPs are associated with the natural course of disease in general. If, however, the estimated association persists, this will suggest that the association is specific to lithium responsiveness. To further confirm this possibility, we will examine the data from the Depakote arm of the Prospective Study. We will test whether the identified SNPs predict clinical relapse or symptom differences among patients who are crossed over to Depakote. If they are not associated, this will suggest the variants are associated specifically with lithium responsiveness.

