### Power

We calculated the power for the survival analysis of the Prospective Study following the methods of Lakatos [55] based on a proportional hazards model and assuming a nominal significance alpha of 0.05. We further assumed a dominant model to simplify the calculations, but note that this model typically provides a conservative estimate of power compared to a log additive model, which is what we plan to assume in the analyses. Finally, we assumed 2 years of follow-up with a relapse rate of 50 % among participants with the wild type genotype. Figure 3 below shows the power of our sample to identify a significant association under these conditions for an estimated sample of 700 patients in the Prospective Study for various hazard ratios and minor allele frequencies.

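### Finding no SNP association in the valproate crossover group is read as support for lithium specificity, without testing whether the two drug effects differ

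*Protocol article*

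**What the plan says.** The Statistics section of the protocol article gives two strategies for judging whether a SNP effect is specific to lithium. The first adds a covariate for prior episode frequency and looks at whether the association survives. The second is offered as further confirmation and uses the crossover patients: "We will test whether the identified SNPs predict clinical relapse or symptom differences among patients who are crossed over to Depakote". The inference from a null result follows: "If they are not associated, this will suggest the variants are associated specifically with lithium responsiveness".

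The Valproate crossover section describes the group: "Participants who are unable to tolerate lithium or fail to achieve relapse prevention on lithium will be crossed over to treatment with valproic acid". It gives the purpose, a check on whether the same SNPs also predict how patients do on valproate, as follows: "Measurement of valproate response in a subset of subjects will make it possible to test whether SNPs associated with lithium response are also associated". No group size is stated. Two features make the group smaller than the lithium cohort. Specific aims allows a patient who relapses to be discontinued instead of crossed over. Those who do cross over must pass new stabilization and observation phases before valproate relapse prevention begins.

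The only power statement (Power section and the Fig. 3 caption) is for all 700 patients on lithium: about 80 % for a hazard ratio of 1.4.

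**The concern.** A significant result in one group and a non-significant result in another do not show that the effects differ. When the second group is smaller, a null result there can be likely even if the SNP acts identically on both drugs. The rule then counts low power as evidence for specificity: the fewer valproate patients followed, the more often it favours that reading.

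Selection adds a second difficulty. Many crossover patients are there because they relapsed on lithium, which is the outcome the SNP was found to predict. A SNP association within that group is conditional on lithium failure or intolerance and cannot be taken at face value.

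The Discussion treats separating a gene effect from natural course as a central design problem and rules out a placebo arm. That leaves covariate adjustment and this crossover step to support the distinction, so a step that leans towards one answer weakens the interpretation of any SNP found.

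**Working it through.** **Inputs from the Power section.** "assuming a nominal significance alpha of 0.05" (sidedness not stated; two-sided taken here). "We further assumed a dominant model to simplify the calculations". "we assumed 2 years of follow-up with a relapse rate of 50 % among participants with the wild type genotype". Lithium sample 700, benchmark HR 1.4.

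**Assumed, because the text gives no figure.** Minor allele frequency (MAF) 0.2-0.3, with 0.10 as a less favourable case. Valproate maintenance group of 100 to 385 patients. Same wild-type relapse rate on valproate as on lithium.

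**Formulas.** Carrier share q = 1 − (1 − MAF)². Expected relapses D = N × [(1 − q) × 0.5 + q × (1 − 0.5^HR)]. Schoenfeld power = Φ(√(D·q·(1 − q)) × |ln HR| − 1.96).

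**The plan's own figure.** For N = 700 and HR 1.4, power is 71 % at MAF 0.10, 79 % at 0.13, 81 % at 0.14, 88 % at 0.20 and 92 % at 0.30. The stated 80 % is matched at MAF of about 0.13-0.14. The same inputs imply about 366 to 393 relapses on lithium (MAF 0.10 to 0.30). The 385-patient case therefore corresponds to nearly every lithium relapser reaching valproate maintenance.

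**One case in full: N = 200, MAF 0.20, HR 1.4.** q = 0.36. Carrier relapse = 1 − 0.5^1.4 = 0.621. D = 200 × (0.64 × 0.5 + 0.36 × 0.621) = 108.7. √(108.7 × 0.36 × 0.64) = 5.005; times ln 1.4 = 0.3365 gives 1.684. Power = Φ(1.684 − 1.96) = 39 %. An observed HR of exactly 1.4 would have a 95 % CI of 0.95 to 2.07 and would be read as not associated.

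**Power on relapse for the same HR of 1.4 on valproate:**

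| Valproate patients | MAF 0.10 | MAF 0.2-0.3 |
|---|---|---|
| 100 | 16 % | 22-24 % |
| 150 | 21 % | 31-34 % |
| 200 | 27 % | 39-43 % |
| 250 | 33 % | 47-51 % |
| 350 | 43 % | 61-65 % |
| 385 | 47 % | 65-70 % |

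**A check that needs no MAF.** The plan's 80 % at 700 corresponds to a standardized effect of 1.96 + 0.84 = 2.80. Scaled by √(N/700), it becomes 1.98 at 350, 1.67 at 250 and 1.30 at 150, giving power of about 51 %, 39 % and 25 %.

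**Sensitivity with 250 patients, MAF 0.2-0.3.** HR 1.6: 76-81 %. HR 2.0: 98-99 %. HR 1.4 with 70 % wild-type relapse: 59-64 %.

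**The direct contrast.** Suppose HR is 1.4 on lithium (385 events) and 1.0 on valproate (D₂ events). Treating the two estimates as independent, SE = √(1/(385·q(1 − q)) + 1/(D₂·q(1 − q))). With D₂ = 55 and MAF 0.20, SE = 0.300 and power = Φ(0.3365/0.300 − 1.96) = 20 %. With D₂ = 140 and MAF 0.30, SE = 0.197 and power is 40 %.

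**The case against.** The wording is cautious. The plan says a null result would suggest specificity, places the step after the covariate analysis, and the Discussion claims only some scope for comparison. A reader might infer that the plan treats the null as proof; the text does not say that.

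A reader might also turn the table into an error rate, for example that with 100-250 patients a shared SNP is called lithium-specific 49-78 % of the time (100 minus 51 and 22). The document does not support that. The rule covers relapse or symptom differences, so a shared SNP has a second chance of detection through the repeated measures, and the covariate step may already have removed some natural-course SNPs. The figures are miss rates for relapse alone at one effect size.

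The dominant model is described as conservative against the planned log-additive one. For a per-allele HR of 1.4, replacing q(1 − q) by 2·MAF·(1 − MAF) and keeping the event counts for 250 patients (135.9 and 140.4), power is Φ(√(135.9 × 0.32) × 0.3365 − 1.96) = 60 % at MAF 0.20 and Φ(√(140.4 × 0.42) × 0.3365 − 1.96) = 73 % at MAF 0.30. That is better, but still a sizeable miss rate.

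The group size is an assumption. It is not established that the group will be small in absolute terms, only that it is a subset. Nor was everyone in it selected on relapse, since intolerant patients also cross over. Finally, the primary Cox analysis and the sample size are unaffected, and power for a secondary group may sit in an analysis plan not shown.

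These points limit the size of the problem but do not remove it. The inference is printed in the protocol, so it is not a detail left for later, and nothing in it compares the two effects.

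**Conclusion.** The point holds in this form: absence of association in the crossover group is taken to support lithium specificity although the difference between drugs is never tested. For a SNP whose true effect is the plan's benchmark HR of 1.4 on both drugs, relapse data would miss it in roughly half to three-quarters of cases with 100-250 valproate patients, and in about 30-35 % of cases even with 385 (MAF 0.2-0.3). At MAF 0.10 the miss rate is higher throughout.

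This rests on the assumed group sizes and allele frequencies, two-sided testing and equal relapse rates on the two drugs. It applies to effects near HR 1.4: at HR 1.6 to 2.0 with 250 patients power is adequate. Selection on lithium failure or intolerance is a separate limitation, and the document gives nothing from which to work out its size.

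A side point concerns who is in the group. The Valproate crossover section sends patients who cannot tolerate lithium to valproate, while Dosing says: "Patients who cannot tolerate 300 mg/day of lithium will continue to receive TAU" and otherwise follow the protocol. The two can perhaps be read together, but they should be reconciled so that membership is clear. The power argument does not depend on it.

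**What to change.** In the Statistics section:

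- Remove the inference from no association to specificity.
- Report the SNP effect on valproate with its 95 % CI, described as conditional on lithium failure or intolerance.
- Estimate the lithium-minus-valproate difference in SNP log hazard ratio in one model, with standard errors clustered by participant (the same people contribute to both periods), and give its 95 % CI.
- State that the data support a difference between drugs only if that interval excludes zero; otherwise report 'not distinguishable'.
- Add the caveat that even an interval excluding zero does not remove selection into the crossover group, or the inflation from choosing SNPs for significance on lithium.
- Reconcile Dosing and Valproate crossover on patients who cannot tolerate lithium.

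The cost is a change of wording and one further model on data already planned. The real price is scientific: with about 20-40 % power at 55-140 valproate events the contrast will often be inconclusive, and fewer SNPs can be called lithium-specific.

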### Power

We calculated the power for the survival analysis of the Prospective Study following the methods of Lakatos [55] based on a proportional hazards model and assuming a nominal significance alpha of 0.05. We further assumed a dominant model to simplify the calculations, but note that this model typically provides a conservative estimate of power compared to a log additive model, which is what we plan to assume in the analyses. Finally, we assumed 2 years of follow-up with a relapse rate of 50 % among participants with the wild type genotype. Figure 3 below shows the power of our sample to identify a significant association under these conditions for an estimated sample of 700 patients in the Prospective Study for various hazard ratios and minor allele frequencies.

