### Lithium-mediated gene expression

There are likely hundreds if not thousands of genes that are modulated in some way by lithium. Data have been emerging for the past several years that clearly demonstrate lithium-mediated gene expression changes. Bosetti et al. reported changes in the expression of a variety of genes in response to lithium, including those from signal transduction pathways [28]. The study of a larger gene array with 39,000 transcripts in mice [29] reported 4,474 genes with nominally significant expression changes and 121 with a stringent Bonferroni correction. There were 13 genes affiliated with phosphotidylinositol metabolism, again consistent with the cell signaling pathway hypothesis. One of the more comprehensive studies reported to date used a human neuronal cell line (SK-N-AS), and they reported 347 upregulated and 324 downregulated genes, from 3 primary pathways: the mitogen-activated protein kinase (MAPK) signaling pathway, an actin cytoskeleton pathway and a calcium signaling pathway [30].

Expression patterns of micro RNAs (miRNA) in the hippocampus of rats have shown that lithium and valproate both decreased the expression of several miRNAs considered candidates for bipolar disorder; including the pathways involving Wnt/βcatenin [31]. A study of miRNA in lymphoblastoid cell lines found increased expression when exposed to lithium, with a clear variation in expression patterns with time, reflecting the dynamic biological system wherein gene expression is unlikely to be static [32].

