### Statistics

For the analysis of the Prospective Study, we will examine the outcome for lithium response as a time to event, where the event is defined as clinical relapse as defined above. For this we will use Cox Proportional Hazards models of the form:$$ \log\ \mathrm{h}\left(\mathrm{t}\right) = \upalpha \left(\mathrm{t}\right) + {\upbeta}_1{\mathrm{X}}_1 + \dots + {\upbeta}_{\mathrm{k}}{\mathrm{X}}_{\mathrm{k}} $$

where h(t) is the hazard of relapse at time (t) and the time axis is defined as the time from stabilization on drug to either clinical relapse, censoring due to loss to follow-up or discontinuation of study medication, or the end of the follow-up period. This model is semi-parametric in that the baseline hazard of relapse can take any form, but the covariates enter the model linearly and are assumed to have constant relative hazard over the entire time period. This assumption of constant relative hazard over time can be evaluated (and remedied if needed) by including in the model interactions terms between the covariate of interest and time. Building on this framework, we will test in separate models whether the SNPs identified in the ConLIGen Retrospective Study are significantly associated with the relative hazard of clinical relapse. We will include in the models covariates for age, sex, clinical site, and up to 10 quantitative indices of ancestry (if preliminary analyses of the genetic data suggest evidence of population stratification in the sample) to control for the potential confounding effects on these associations. We will also be able to include a covariate for an indicator variable capturing whether the patient entered the prospective study already on lithium as allowed by the protocol in order to control for this as well as to test whether associations differ for these versus other patients.

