**Fig. 3 Fig3:**
[figure not shown]
Power of survival analysis as a function of hazard ratio and allele frequency for 700 subjects. Power analyses indicate that a sample of 700 subjects will have about 80 % power to detect a hazard ratio of 1.4

As described above, we plan a two-stage analysis in which a small number of a priori hypotheses will be tested in stage 1 so as to preserve power. SNPs to be tested in this stage will be selected from our collaborating retrospective lithium study, ConLiGen, significant SNPs from our retrospective sample, SNPs reported in the literature and those selected from expression studies of iPSC-derived neurons. In a second stage of analysis, a full GWAS will be conducted as an exploratory analysis to discover novel variants that may be replicated in other samples.

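### The only stated power, about 80 % at hazard ratio 1.4, is for one SNP at alpha 0.05 and does not carry over to the multi-SNP stage 1 that the plan describes

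*Protocol article*

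**What the plan says.** The Power section uses the Lakatos method under proportional hazards, "assuming a nominal significance alpha of 0.05". It takes a dominant genetic model to simplify the calculation, adding that this is usually conservative compared with the log-additive model planned for the analysis. It further states that "we assumed 2 years of follow-up with a relapse rate of 50 % among participants with the wild type genotype". The results are plotted "for an estimated sample of 700 patients in the Prospective Study for various hazard ratios and minor allele frequencies". The legend of Fig. 3 concludes that "a sample of 700 subjects will have about 80 % power to detect a hazard ratio of 1.4".

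The text directly after the legend sets out two stages. First, "a small number of a priori hypotheses will be tested in stage 1 so as to preserve power"; these SNPs come from ConLiGen, the group's own retrospective sample, the literature and the iPSC expression work. A full GWAS follows and is labelled exploratory.

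The Statistics section fits separate Cox models when it tests the ConLiGen SNPs. Specific aims presents the selective first testing of ConLiGen SNPs as a way to control multiple comparisons. The article gives no number of stage-1 SNPs, no corrected alpha and no power at a corrected alpha.

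**The concern.** A power figure at alpha 0.05 describes the chance of detecting one SNP named in advance. Stage 1 is a family of tests. One of two things then follows:

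- If stage 1 is corrected for multiplicity, as Specific aims implies, the bar for each SNP rises and power at hazard ratio 1.4 falls below the published value.
- If each SNP is tested at 0.05, the per-SNP power stands but the family-wise error does not.

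This is the only power statement offered for the sample of 700. A reader who sets a null stage-1 result against 80 % power at hazard ratio 1.4 would give that result more weight than it deserves.

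**Working it through.** **Inputs from the Power section and the Fig. 3 legend.** N = 700; hazard ratio (HR) 1.4; 50 % relapse at 2 years in wild type; dominant model; alpha 0.05.

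**Assumptions.** Two-sided test (sidedness is not stated); exponential hazards; no loss to follow-up; Hardy-Weinberg proportions; Schoenfeld approximation in place of Lakatos; K and the MAF varied.

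**Step 1: reproduce the plan's figure (one SNP, dominant model).**

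- Carrier share: c = 1 − (1 − q)², where q is the MAF.
- Events: D = 700 × [(1 − c) × 0.5 + c × (1 − 0.5^1.4)], with 0.5^1.4 = 0.379.
- Power = Φ(√(D·c·(1 − c)) × ln 1.4 − z), where ln 1.4 = 0.3365 and z = 1.960 at alpha 0.05.

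At q = 0.134, c = 0.250 and D = 371, so √(371 × 0.250 × 0.750) × 0.3365 = 2.81 and power = Φ(2.81 − 1.96) = 80 %. Other values are 71 % at MAF 0.10, 88 % at 0.20 and 92 % at 0.30. The published 80 % is thus reproduced for a single test at MAF about 0.13.

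**Step 2: correct from the stated 80 %.** This step needs no MAF. The implied noncentrality is 1.960 + 0.842 = 2.802. With K SNPs tested at 0.05/K, power = Φ(2.802 − z(1 − 0.05/2K)).

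| K (assumed) | critical z | power | HR detectable with 80 % power |
|---|---|---|---|
| 1 | 1.960 | 80 % | 1.40 |
| 4 (one per source) | 2.498 | 62 % | 1.49 |
| 10 | 2.807 | 50 % | 1.55 |
| 100 | 3.481 | 25 % | 1.68 |

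The detectable HR is exp[ln 1.4 × (z + 0.842)/2.802], holding the information fixed.

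**Step 3: the most favourable case under the dominant model.** At MAF about 0.30, c = 0.51, D = 393 and the noncentrality is 3.335. Power is 80 % for 4 SNPs, 70 % for 10 and 44 % for 100.

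**Step 4: the planned log-additive model.** A per-allele HR of 1.4 is assumed. Genotype variance is 2q(1 − q), and D = 700 × [(1 − q)² × 0.5 + 2q(1 − q)(1 − 0.5^1.4) + q²(1 − 0.5^1.96)]. At q = 0.20, D = 384, so √(384 × 0.32) × 0.3365 = 3.73. With K = 10, power = Φ(3.73 − 2.807) = 82 %.

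| MAF | K = 10 | K = 100 |
|---|---|---|
| 0.10 | 47 % | 23 % |
| 0.20 | 82 % | 60 % |
| 0.30 | 94 % | 81 % |

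**Step 5: no correction.** With independent null SNPs each tested at 0.05, the chance of at least one false hit is 1 − 0.95^K: 19 % for 4, 40 % for 10 and 64 % for 20.

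**The case against.** The strongest reply is that nothing has been miscalculated. The 80 % reproduces, the alpha is openly called nominal, and stage 1 is kept short precisely to protect power. Dominance is declared a simplification, and under the log-additive model a short list of common SNPs keeps 80 % or more after Bonferroni (step 4). A condensed article may also leave the SNP list and threshold to an analysis plan. Most of this stands. It makes the loss dependent on K and MAF, and it rules out calling the figure an arithmetic error. It does not close the gap: the legend's conclusion carries no caveat, the multiple tests are described immediately after it, and at MAF 0.10 ten SNPs leave 47 % even under the additive model. The point concerns a published figure that does not match the plan beside it, not a missing detail.

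A reader might infer more than the document supports:

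- **That the trial is underpowered for its GWAS.** Stage 2 is exploratory and no power is claimed for it.
- **That the stage-1 list must be long because the background reports "347 upregulated and 324 downregulated genes".** Those 671 genes come from another group's cell-line experiment. The plan's filter is narrower: genes changed in responders but not in non-responders.
- **That the 80 % has no allele frequency attached.** Fig. 3 plots power by allele frequency and is not reproduced in the text available here.
- **That 30–40 % non-response cuts the 700 to 420–490.** The background gives that as a general non-response rate, not attrition before maintenance, and relapse during maintenance is already the event.
- **That false positives would be near certain without correction.** For 10 to 20 independent null SNPs the chance is 40 % to 64 %.

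**Conclusion.** The point holds. The stated 80 % is correct for one SNP at alpha 0.05 but is not the power of stage 1 as described. Starting from 80 %, Bonferroni power is about 62 %, 50 % and 25 % for 4, 10 and 100 SNPs. At the best MAF under the dominant model, 80 % survives only up to about four SNPs. Under the planned log-additive model the shortfall is mainly at lower MAF or with longer lists.

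These sizes rest on assumed values of K, two-sided testing, no loss to follow-up, Bonferroni as the form of control, and, for the additive figures, a per-allele HR of 1.4. A false discovery rate (FDR) rule or correlated SNPs would soften the loss. Specific aims states the intention to control multiple comparisons but names no method. If none is applied, the cost moves from power to the false-hit rates in step 5.

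**What to change.** 1. Freeze the stage-1 list, and so K, before any analysis relates outcome to genotype.
2. Test stage 1 at 0.05/K or at a stated FDR.
3. Label the 80 % in the Power section and the Fig. 3 legend as power per SNP before multiplicity correction.
4. Add power, or the hazard ratio detectable with 80 % power, by MAF at the stage-1 threshold under the log-additive model that will be used.
5. Leave stage 2 exploratory, with no power claim.

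The cost is some wording and one rerun of the power table. No additional participants are needed. The price is a less favourable headline figure at lower MAF or with longer lists, and the loss of freedom to add candidates to stage 1 once outcome has been related to genotype.
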